
### Measures to be collected from healthy control group

The healthy control group will be matched to the HF patient group on age, premorbid intelligence and gender, and will undergo neuropsychological assessment as described above and highlighted with asterisks in Table 1. Psychosocial demographics, including social support and anxiety and depression, will also be collected to allow comparisons of the healthy controls and HF participants.

### Additional patient outcome measures

There will be 3 additional outcome measures of self-care collected at Assessments One (2 to 4 weeks post cognitive training) and Two (12 months post cognitive training):

The first is patient engagement in self-care. On enrolment into the study, HF patients will be provided with a symptom monitoring diary by the research assistant who will explain how to use them. At Assessments One and Two the research assistant will review whether the diaries have been completed. The research assistant will also collect practical data on how the HF patient performs daily weighing, monitors their fluid intake; reads food labels to determine the sodium content of food; and follows their prescribed medication regimen.

The research assistant will ask the HF nurse caring for the patient participant to complete a questionnaire to assess the nurses’ perception of the patient’s engagement in HF self-care.

The *Unplanned Healthcare Utilisation Questionaire* will be used to collect information about unscheduled visits to GP, cardiologist, HF nurse and emergency department. Information about survival will be collected from hospital records.

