## Methods/design

### Study design

This will be a randomised controlled trial where 200 patients with HF will be randomised to receive either: 1) the Virtual Week Training Program, a computerised adaptively difficult PM training program, or 2) non-adaptive computer-based word puzzles. Sixty healthy control participants, with no HF diagnosis, will also be assessed to compare differences in baseline measures of cognitive and psychosocial functioning. There are 4 phases to the study: 1) baseline testing; 2) 6 weeks of cognitive training; 3) Assessment One, 2 to 4 weeks post cognitive training; and 4) Assessment Two, 12 months post cognitive training. There will be two separate interviews during each of the assessments (baseline testing, Assessment One and Assessment Two). These will be: a) nursing assessment including physical functioning, and self-care; and b) PM and neurocognitive assessment, and TIADL.

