### Participant inclusion criteria

A total of 200 HF patients aged 18 years or older will be recruited. Inclusion criteria will be: diagnosis of HF with reduced ejection fraction (ejection fraction < 45% in the previous 2 years) as confirmed by a cardiologist and consistent with Australian guidelines [34]; attendance at a specialist HF clinic or rehabilitation program, and/or a disease management program with nursing follow-up and able to participate in the study (that is adequate vision, hearing and English comprehension). Carers will be identified by HF patients as someone who is familiar with and contributes to the management of their heart condition (for example, a partner, family member, friend or next of kin). Patients who cannot identify a carer will still be eligible to participate in the study. All HF patients enrolled in the study will continue to receive usual care which can be from any combination of nurse-led chronic disease management programs, specialised HF outpatient clinics, or outpatient rehabilitation programs. A key aspect of usual care is patient education and support from a multidisciplinary team that is directed at promoting self-care maintenance and monitoring behaviours. Healthy control participants will be living independently in the community without a medical diagnosis of HF and have adequate performance on the Addenbrooke’s Cognitive Examination Revised (ACE-R) [35].

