### Recruitment

Participants will be recruited over a 24-month period, or until the required sample size is achieved. A HF nurse will initially assess patients’ eligibility to participate in the study: those who meet the inclusion criteria will be referred to the study research assistant who will approach potential participants at their outpatient appointment, explain the study (both verbal and written information), and obtain their consent. They will be asked to identify if they have an informal carer or next-of-kin who would be willing and able to complete some questionnaires for the study. A research assistant will contact the carer, explain the study and their involvement, obtain consent and collect baseline questionnaires. Healthy control participants will be sourced from the community by advertisements in local newspapers and word-of-mouth. Research assistants will screen control participants for study eligibility, explain the study and obtain their consent to undergo the neurocognitive testing. Healthy control participants will be matched to HF patients according to age, premorbid intelligence and gender.

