**Table 1 Tab1:** **Assessment measures at baseline and post-intervention evaluations**

**Measures**	**Baseline**		
		**Assessment One** ^**b**^	**Assessment Two** ^**c**^
Physical functioning			
Physical examination (BP/HR/RR/weight/NYHA class, BNP)	X	X	X
Echocardiogram	X		X
‘Up and Go’ test	X	X	X
Timed Instrumental Activities of Daily Living (TIADL)	X	X	X
Unplanned readmission/survival		X	X
Self-care			
Heart-FaST	X		X
Patient engagement in self-care: (SCHFI and four consulting items from the EHFScBS)	X	X	X
Nurses and carer assessment of patient engagement in self-care	X	X	X
Review of patient symptom monitoring diary and how they perform self-care maintenance behaviours		X	X
Control Attitudes Scale - Revised (CAS-R)	X	X	X
Psychosocial functioning			
Quality of life (SF-12)^a^	X	X	X
Dyadic HF care typology	X		
Hospital Anxiety and Depression Scale (HADS)^a^	X	X	X
Cognitive functioning for HF patients			
Cognitive screen (MoCA)^a^	X	X	X
Assessment of PM (MIST, brief version of Virtual Week and naturalistic task)^a^	X	X	X
Working memory, executive functioning, verbal memory (CogState, N-Back, Trail Making Test)^a^	X	X	X
Premorbid intelligence (NART)^a^	X		
Caregiver			
Health screening questionnaire	X		
Caregiver (or next of kin) Contribution to Self-Care (CC-SCHFI)	X	X	X
Control Attitudes Scale - Revised (CAS-R)	X	X	X
Dyadic HF care typology	X		
Quality of life (SF-12)^a^	X	X	X
Modified Caregiver Strain Index (MCSI)	X	X	X
Proxy - IADL	X	X	X

Key: BNP, brain natriuretic peptide; BP, blood pressure; CC-SCHFI, Caregiver Contribution Self-Care Heart Failure Index; EHFScBS, European Heart Failure Self-care Behaviour Scale; Heart-FaST, Heart Failure Self-care Screening Tool; HF, heart failure; HR, heart rate; IADL, Instrumental Activities of Daily Living; MIST, Memory for Intentions Screening Test; MoCA, Montreal Cognitive Assessment; NYHA class, NART; National Adult Reading TestNew York Heart Association Classification; PM, prospective memory; RR, respiratory rate; SCHFI, Self-Care Heart Failure Index; SF-12, Short-Form 12-item health survey.

^a^Measures will also be collected from healthy non-HF controls at baseline; ^b^2 to 4 weeks post cognitive training; ^c^12 months post cognitive training.

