### Outcomes

Primary study outcomes are patient engagement in HF self-care behaviours from both self-report (SCHFI) and the objective assessments from the carer, researcher and nurse, described above. Secondary outcomes are those not directly related to HF self-care behaviors but relevant to HF: quality of life; BNP, ‘Up and Go’ test, hospital readmissions, survival and transfer effects. To examine near to far transfer effects of the cognitive training we shall use PM tests aligned (or similar) to the training task, MIST and Virtual Week for near transfer effect. To examine for far transfer effects we will reassess overall cognitive function at Assessments One and Two. The TIADL and naturalistic PM task will assess transfer to everyday functioning, and will potentially represent somewhere between near and far transfer.

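### The nurse rating is a primary self-care outcome, but a treating heart failure nurse is not guaranteed at 12 months, and the planned mixed ANOVA would drop patients with one missing rating

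*Protocol article*

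**What the plan says.** All references are to the protocol article.

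- **Outcomes:** the primary outcomes are self-reported self-care (SCHFI) together with "the objective assessments from the carer, researcher and nurse, described above".
- **Additional patient outcome measures:** the nurse component is obtained from the treating nurse: "The research assistant will ask the HF nurse caring for the patient participant to complete a questionnaire".
- **Table 1:** the row "Nurses and carer assessment of patient engagement in self-care" is marked at baseline, Assessment One and Assessment Two.
- **Participant inclusion criteria:** patients qualify through "attendance at a specialist HF clinic or rehabilitation program, and/or a disease management program with nursing follow-up". Enrolled patients then continue "usual care which can be from any combination of nurse-led chronic disease management programs, specialised HF outpatient clinics, or outpatient rehabilitation programs". The two intervention sections repeat this for both arms.
- **Study design:** training lasts 6 weeks, Assessment One is 2 to 4 weeks after it, and the last visit is "Assessment Two, 12 months post cognitive training".
- **Statistical analyses:** every measure taken at the three time points gets its own mixed ANOVA, with testing phase (three levels) within patients and training group between patients.
- **Sample size:** the 20% allowance is for intervention refusal and loss to follow-up.

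**The concern.** Three choices made in the article do not fit together. A primary component depends on a rater who belongs to the patient's ongoing care. Eligibility does not require that rater. The analysis needs the rating at all three phases.

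Two things are at stake. The first is selection. Whether a patient still has a treating HF nurse about a year after training is settled after randomisation. If it is related to self-care, the patients who can be rated are no longer a randomised comparison. The second is information. A conventional mixed ANOVA on three phases uses only patients with all three values, so one missing 12-month rating also discards the Assessment One rating, taken within weeks of the end of training. The early comparison would then rest on a subset defined by what happened later.

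**Working it through.** **Step 1: is the rater guaranteed?**

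- *At entry.* Nursing follow-up is named with the disease management route, and usual care may be "any combination of nurse-led chronic disease management programs, specialised HF outpatient clinics, or outpatient rehabilitation programs". Nurse-led care is one of three services. An HF nurse does the eligibility check ("A HF nurse will initially assess", Recruitment), but that is contact at entry.
- *At Assessment Two.* Training takes 6 weeks and Assessment Two is 12 months after it, so about 6 + 52 = 58 weeks after training starts. Nothing requires a patient to be under an HF nurse then.
- *A study nurse instead?* Study design schedules a nursing assessment, including self-care, at each assessment. The article does not name it as the source of this questionnaire.

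So the design permits a retained patient without a nurse rating. It does not show how many there will be.

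**Step 2: the plan's own sample size.** The 63 per group for 80% power at 0.05 reproduces if the small to medium effect is read as d = 0.5, two-sided:

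n = 2(1.960 + 0.842)² / 0.5² = 62.8, rounded up to 63.

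The noncentral t distribution gives 79.5% at 63. The claim of more than 90% with 200 patients also holds (ANCOVA F test, one covariate): 94.0% at f = 0.25, above 99.9% at f = 0.4, about 100% at f² = 0.4. None of these figures is disputed.

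**Step 3: what missing nurse ratings would cost.**

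From the document: 100 per arm and a 20% allowance, so 100 × 0.80 = 80 retained per arm. Assumed: the share rated and the effect size. Power is that of a two-sided two-sample t-test at 0.05 with 2n − 2 degrees of freedom and noncentrality d√(n/2).

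| Share rated | n per arm | Power, d = 0.5 | Power, d = 0.8 |
|---|---|---|---|
| 100% | 80 | 88% (0.5√40 = 3.16) | 99.9% |
| 70% | 56 | 75% (0.5√28 = 2.65) | 98.7% |
| 50% | 40 | 60% (0.5√20 = 2.24) | 94% (0.8√20 = 3.58) |

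**Step 4: what the mixed ANOVA adds.** Suppose all 80 per arm are rated at baseline and Assessment One, and only 70% at Assessment Two. Complete-case ANOVA then removes 80 − 56 = 24 patients per arm from both follow-up visits; at 50% it removes 40. A likelihood-based model keeps their Assessment One ratings.

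**Step 5: selection, as an illustration.** Assume a true difference of 0.5 SD, and that patients with worse self-care are more likely to be still under a nurse, by the same rule in both arms. With a logit slope of 0.5 to 1.5 per SD, the difference among rated patients is 0.36 to 0.48 SD. With no dependence on self-care it stays at 0.50. A rule that differed between arms could move the difference either way. Every selection input here is assumed.

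**The case against.** The strongest reply is that the gap is possible but not shown. No section says that specialist HF clinics or rehabilitation programs lack HF nurses. The phrase about nursing follow-up could be read with more than the last item in its list. Usual care is multidisciplinary and is said to continue for all enrolled patients, and a nursing assessment is scheduled at every visit. This stands against any claim that the rating cannot be scored for some patients. It does not supply a guarantee.

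A reader might also infer that stable, well-managed patients are discharged from nurse care, so that the effect is biased toward zero. The article gives no discharge rule and no duration of nurse follow-up. That unscheduled HF nurse visits are collected as an outcome shows that nurse contact may vary after randomisation, not that routine nurse care ends.

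A reader might infer that the trial is underpowered. The Sample size section powers standardised self-care maintenance and management scores, which match SCHFI subscales, and not the nurse rating. At larger effects the loss of power is small.

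Finally, naming a substitute rater is detail that an article may leave to a fuller document. That is fair, and no such omission is counted here. What remains is the fit between three things the article does state: the rater, the eligibility rule and the ANOVA.

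**Conclusion.** The point holds as a mismatch in the design that the analysis can ease. A primary component depends on a treating HF nurse whom the article does not guarantee, least of all at Assessment Two. The presence of a rating there is a post-randomisation state that may be related to self-care. The stated ANOVA, run conventionally, makes one missing rating cost the whole patient.

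The size is not known. The power figures for d = 0.5 and d = 0.8 are illustrations that rest on an assumed share rated, an assumed effect and 80 retained per arm. They concern this component only, not the SCHFI. The documents do not fix the direction of any bias.

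The documents do not require that the nurse rating lose its primary status. That is a design choice for the sponsor, in a registered trial that is already recruiting, and it is not part of this finding.

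**What to change.** **In Statistical analyses**, replace the mixed ANOVA for the nurse rating with a likelihood-based repeated-measures model of Assessments One and Two. Include arm, visit and their interaction, adjust for the baseline nurse rating, and keep every patient with at least one post-baseline rating. A patient whose baseline rating is missing can be kept by entering baseline as a further response with the arm means constrained equal.

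**In Additional patient outcome measures**, which mentions only the two follow-up assessments, confirm the baseline nurse rating that Table 1 schedules. Add two recorded fields: whether the patient has an HF nurse, taken at baseline before randomisation; and the date of the nurse's last contact with the patient, at each rating.

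**In reporting**, give the number rated by arm and visit. If many Assessment Two ratings are missing, or the numbers differ by arm, interpret the Assessment Two nurse comparison as supportive.

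**Cost:** a little more analysis work and one or two recorded fields. The model relies on missingness at random given the baseline and Assessment One ratings. It does not remove selection that depends on unobserved 12-month self-care, which is why the counts and the interpretation rule are needed.

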### Outcomes

Primary study outcomes are patient engagement in HF self-care behaviours from both self-report (SCHFI) and the objective assessments from the carer, researcher and nurse, described above. Secondary outcomes are those not directly related to HF self-care behaviors but relevant to HF: quality of life; BNP, ‘Up and Go’ test, hospital readmissions, survival and transfer effects. To examine near to far transfer effects of the cognitive training we shall use PM tests aligned (or similar) to the training task, MIST and Virtual Week for near transfer effect. To examine for far transfer effects we will reassess overall cognitive function at Assessments One and Two. The TIADL and naturalistic PM task will assess transfer to everyday functioning, and will potentially represent somewhere between near and far transfer.

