### Hypotheses

We hypothesise that the cognitive training will result in improved functioning, better health outcomes and reduced healthcare costs in this patient group. In addition, we predict that the improved functioning of the HF patients will reduce levels of carer burden (strain, perceived control, contribution to patient HF self-care) and improve their quality of life.

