I.*Patient clinical and socio-demographics*: age, gender, education level, social support, employment history. Patient clinical history, blood pathology (B-type natriuretic peptide (BNP), urea, electrolytes, full blood count), echocardiographic assessment of left ventricular systolic and diastolic function and assessment of valvular function, HF aetiology and treatments (medications, devices, surgery), physical examination (heart rate, blood pressure, respiratory rate, weight).II.*Heart Failure Screening Tool* (Heart-FaST) [36]: assesses three functional domains salient to patient engagement in self-care: physical, cognitive and emotional functioning. Higher scores on each barrier scale indicate worse functioning. Preliminary analyses support the construct validity of the Heart-FaST as a screening tool for physical, cognitive and emotional barriers that may hinder engagement in HF self-care. Heart-FaST, therefore, has the potential to assist clinicians in tailoring educational and surveillance disease management strategies to individual need [37].III.*Self-Care Heart-Failure Index* (SCHFI) [38]: assesses HF self-care behaviours and skills comprising 15 items rated on a 4-point scale to measure the process of self-care. There are three sub-scales: maintenance, management and confidence. Responses from each of the 3 self-care scales are transformed to a 100 point scale; higher scores reflect superior self-care. Self-care management scores are only computed for those patients reporting HF symptoms of ankle swelling or trouble breathing in the previous three months. Scaled scores > 70 are considered adequate self-care [38].IV.*European Heart Failure Self-care Behaviour Scale* (*EHFScBS*) [39,40]: 4 items from this scale will assess consulting behaviours in response to increased dyspnoea, feet swelling, weight gain and fatigue. Scores on the consulting subscale range from 4 to 20 with higher values indicating a lower likelihood of contacting providers for guidance when a change in signs or symptoms suggests worsening HF.V.*The Control Attitudes Scale - Revised* (CAS-R) [41]: assesses cardiac patients’ subjective perceived control in relation to managing their heart condition. Each of the 8 items is measured on a 5-point Likert scale ranging from 1 (strongly disagree) to 5 (strongly agree). Internal consistency in the HF population was Cronbach’s α = 0.76, and it showed good construct validity [41]. This scale will be administered to the HF patients, and will be adapted for administration to the caregivers. For example, one item on the CAS-R states: ‘If I do all the right things, I can successfully manage my heart condition’, and will be adapted for caregivers to state: ‘If I do all the right things, I can successfully manage the patient’s heart condition’. Similar amendments have been made in other studies investigating the perceived control of caregivers of patients with cardiac disorders [42,43].VI.*Short-Form 12-item health survey* (SF-12) [44]: assesses quality of life. The health survey consists of 12 items on a Likert response: 1) physical functioning, 2) physical role, 3) bodily pain, 4) general health, 5) vitality, 6) social functioning, 7) emotional role, and 8) mental health. Summary scale scores can be transformed to a scale of 0 to 10, with higher scores representing better health [44].VII.*The ‘Up and Go’ test* [45]: assesses functional mobility; stand from sitting, walk at usual speed for 3 meters, turn and return to sitting. To allow for test effect, an average of two timed trials will be recorded. The test is a measure of balance, walking ability and risk of falling in older populations and has been shown to be consistently reliable in test-retest analysis in patients with chronic conditions, including HF [45].VIII.*Dyadic HF care typology* [46,47]: describes the caregiving relationship between the HF patient and nominated carer. Both the HF participant and their carer will, independently, identify how their relationship functions in terms of managing HF symptoms. Care relationship types have been operationalised into: 1) caregiver responsible for the majority of the care of the HF patient, 2) HF patient responsible for the majority of their own care, 3) caregiver and the HF patient equally responsible for all aspects of the care, or 4) caregiver and the HF patient responsible for different aspects of the care.IX.*Hospital Anxiety and Depression Scale* (HADS) [48]: assesses anxiety and depression. Seven of the 14 items relate to anxiety and 7 relate to depression. Responses are provided on a Likert scale, and scores on each scale are interpreted in ranges: normal (0 to 7), mild (8 to 10), moderate (11 to 14), and severe (15 to 21). The 2 subscales have a mean correlation of 0.56, the mean Cronbach’s α is 0.83 for anxiety and 0.82 for depression [49].X.*Montreal Cognitive Assessment* (MoCA) [50]: screens for mild cognitive impairment in the domains of: visual-spatial skills; executive functions; language; attention; concentration; working memory; memory recall; and orientation. Low educational attainment is corrected by adding 1 point to the participant’s final score for ≤ 12 years of formal education. The highest possible score is 30 and a score 26 and above indicates normal cognitive function [50].

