
### Baseline and follow-up measures to be collected from carers

Carers will be asked to complete seven brief questionnaires:I.A health screening questionnaire will be used to identify the presence of specific health problems (cardiac, metabolic, diabetic, respiratory, muscular, family history, treatment precautions, and physical activity) and will be used for descriptive purposes.II.Carer contribution to HF self-care (CC-SCHFI) [65] is derived from the SCHFI and assesses the career’s contribution to self-care maintenance and management behaviours. This information will be used to provide a more comprehensive assessment of the patient participant’s engagement in self-care.III.Control Attitudes Scale - Revised (CAS-R) [41] will be administered to measure the carer’s perceived control in relation HF management. Each item is measured on a 5-point Likert scale ranging from 1 (strongly disagree) to 5 (strongly agree) and has been shown to have good internal reliability in a HF population (α = 0.76) [41]. This scale has been adapted for administration to the caregivers of patients with cardiac disorders [42,43].IV.Carers will also identify how their relationship with the HF patient functions in terms of managing HF symptoms using the dyadic HF care typology (described above).V.SF-12 will be administered (described above) as an indication of the quality of life of the carer.VI.Modified Caregiver Strain Index (MCSI) assesses the causes, and the degree of strain, and changes in strain over time. It has four domains of strain: financial, physical, psychological and social and personal. The reported internal reliability of the MCSI is high (Cronbach’s α = 0.90) and it correlates with care recipient’s functioning [66,67]. The tool will be administered to monitor changes in carer strain from baseline to 3- and 12-month follow-up.VII.To measure of HF patients’ level of functioning, carers will be asked to indicate the HF participants’ level of independence in daily activities using the validated Instrumental Activities of Daily Living (IADL) Scale [68]. This instrument assesses how much help the individual requires to perform each of eight tasks (using the telephone, shopping, food preparation, housekeeping, laundry, transportation, managing medications and home finances). A score of 1 indicates ‘no help’, and higher scores indicate increased dependence. Performing instrumental daily activities successfully requires a high level of skill and judgment: therefore, greater dependency is likely to be sensitive to mild changes in cognitive capacity [69].

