### Statistical analyses

To compare and confirm cognitive deficits, including PM, between HF patients and a healthy matched control, group differences in baseline PM and neuropsychological tests will be examined using inferential statistics (*t*-test and analysis of variance; ANOVA). To analyse the changes in each measure assessed at each time point (baseline, Assessment One and Assessment Two) we will use separate mixed ANOVAs for all dependent variables. The within-groups variable will be *testing phase* (baseline, Assessment One, Assessment Two) and the between-groups variable will be *Training group* (PM training, word puzzles). Multiple regression analysis will be performed to identify whether physical, cognitive, emotional and mental functioning variables are independent predictors of HF self-care and consulting behaviours, after adjusting for clinical characteristics. For all analyses, α levels will be set at 0.05 and effects sizes will refer to partial η-square values.

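### Self-care scores from four sources are co-equal primary outcomes, each tested at 0.05 with no lead score, visit or success rule, and the carer score is not clearly identified

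*Protocol article*

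**What the plan says.** The Outcomes section of the protocol article reads: "Primary study outcomes are patient engagement in HF self-care behaviours from both self-report (SCHFI) and the objective assessments from the carer, researcher and nurse". The wording is plural. No composite, order of testing, deciding visit or number of required successes is given.

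The four sources can yield more than four scores. For the SCHFI, item III of the patient measures says "There are three sub-scales: maintenance, management and confidence" and describes no total. It adds: "Self-care management scores are only computed for those patients reporting HF symptoms of ankle swelling or trouble breathing". The researcher's source (Additional patient outcome measures) is a diary check plus several practical observations without a stated score, and Table 1 shows no baseline for it.

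Statistical analyses says "we will use separate mixed ANOVAs for all dependent variables", with testing phase as one three-level within-groups factor and training group between groups. It closes with "For all analyses, α levels will be set at 0.05" and states no adjustment. Sample size refers to one primary endpoint, assumes ANCOVA, and uses the self-care maintenance and management scores.

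On the carer, the only self-care instrument among the seven carer questionnaires is the CC-SCHFI, which "assesses the career’s contribution to self-care maintenance and management behaviours". The same item says it will help to assess the patient's own engagement. Hypotheses predicts that better patient functioning will "reduce levels of carer burden (strain, perceived control, contribution to patient HF self-care" and so places that contribution under burden. Inclusion criteria add: "Patients who cannot identify a carer will still be eligible to participate in the study".

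**The concern.** A set of equally ranked primary scores, each tested at the full 0.05, gives the trial several chances to declare primary success when training has no effect. The 0.05 level would protect the overall claim only if a single score decided, or if every score had to succeed. The article says neither. Outcomes and Sample size also disagree on what is primary: four sources in one, two SCHFI subscales in the other. After the data are in, whichever score reached significance could be presented as the primary result.

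The carer source raises a second, separate question of validity. If the primary carer score is the CC-SCHFI, a fall could be read as good (less load on the carer) or as bad (less self-care being done). A primary outcome needs one favourable direction, fixed in advance.

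**Working it through.** **Step 1. The plan's own figure.** Sample size claims more than 90% power with 100 per group, α = 0.05 and f² = 0.4. Using a noncentral F with 1 numerator df, one covariate and λ = N × f²:
- N = 200: λ = 200 × 0.4 = 80, power about 100%.
- N = 160 (200 × 0.8, after the stated 20% loss): λ = 64, power about 100%.

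The claim holds as an inequality. It concerns one test at 0.05 and says nothing about a family of tests.

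**Step 2. How many tests.** Each score has one mixed ANOVA with phase as a single factor. Taking the group-by-phase interaction as the deciding effect (the article does not say which effect decides) gives one test per score. Three counts are considered:
- K = 2: SCHFI maintenance and management, as in Sample size.
- K = 4: one score per source.
- K = 6: three SCHFI subscales plus carer, researcher and nurse (3 + 1 + 1 + 1).

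**Step 3. Independent tests.** P(at least one false positive) = 1 − (1 − 0.05)^K.
- K = 2: 1 − 0.95² = 0.0975
- K = 4: 1 − 0.95⁴ = 1 − 0.8145 = 0.185
- K = 6: 1 − 0.95⁶ = 1 − 0.7351 = 0.265

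**Step 4. Correlated tests.** Scores of the same behaviour will be correlated, but the article gives no correlations, so a range is assumed. The correlated columns come from a simulation of 400,000 draws of K equally correlated two-sided z-tests. The interaction itself has 2 numerator df, so these columns are approximate.

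| K | Independent | r = 0.3 | r = 0.5 | r = 0.7 |
|---|---|---|---|---|
| 2 | 9.8% | 9.5% | 9.1% | 8.4% |
| 4 | 18.5% | 17.3% | 15.6% | 13.1% |
| 6 | 26.5% | 24.1% | 20.8% | 16.5% |

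For four to six scores the rate is 13.1/5 = 2.6 to 26.5/5 = 5.3 times nominal.

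**Step 5. Visits.** The mixed ANOVA does not test each visit separately. The ANCOVA in Sample size could be run at each visit, and the researcher's review cannot enter a three-phase ANOVA without a baseline, so per-visit testing is left open. If it were done, four scores at two visits (8 tests) would give 33.7% if independent and 25.0% at r = 0.5. Six scores at two visits (12 tests) would give 46.0% and 32.0%.

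**Step 6. What control would cost.** The strictest Holm step is 0.05/4 = 0.0125 or 0.05/6 = 0.0083. At f² = 0.4, power at these levels stays about 100%. At an assumed smaller effect of f = 0.25 and N = 160, power for one ANCOVA is 88.2% at 0.05, 73.7% at 0.0125 and 68.8% at 0.0083. With N = 200 it is 94.0%, 84.4% and 80.7%.

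**Step 7. The carer passages side by side.**
- Carer measures, item II: the CC-SCHFI records what the carer contributes, and is to inform patient engagement.
- Study aims and Hypotheses: that contribution is listed under carer burden.
- Background: burden is defined by strain, perceived control and quality of life, without contribution.
- Abstract and Table 1: carers rate the patient's engagement. Table 1 puts this on its own row, apart from the CC-SCHFI, but the carer section describes no such instrument.
- Inclusion criteria: patients without a carer are eligible, so a carer score cannot exist for them.

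The primary carer score therefore cannot be identified with certainty, nor can its favourable direction.

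**The case against.** The strongest reply is that multiplicity rules and test order usually sit in a SAP, which is not shown. That would excuse silence, but the article is not silent: it sets 0.05 for all analyses and names several primaries.

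The score count is also open to challenge. Outcomes speaks of behaviours, so the SCHFI confidence subscale may not be intended as primary, and the researcher's data could yield no score or several. This stands, and is why the result is a range. The lowest count, two scores, still nearly doubles the nominal rate.

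Three stronger readings are tempting and are not supported:
- **Twelve separate primary tests and a 46% error rate.** The stated model enters the visits as levels of one factor, so 12 is not the plan's literal count. It applies only if each visit is tested separately.
- **A chance success is likely.** Every scenario computed is below 50%. Materially inflated is what the figures bear out.
- **The CC-SCHFI is really a carer-burden measure.** Its own description gives it a role in assessing the patient, Background leaves contribution out of burden, and the Abstract and Table 1 list a distinct carer rating. The list in Hypotheses also contains perceived control, whose reduction would hardly be a benefit, so it does not firmly predict a fall in contribution. Study aims speaks only of change.

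Nor does the carer problem raise the chance-success rate. It concerns validity and direction, and is separate from multiplicity.

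**Conclusion.** The concern holds as a material inflation of the primary false-positive rate, written into the article by several unranked primary outcomes and a 0.05 level for every analysis. For four to six scores with one test each, the rate is about 13% to 26%, depending on correlation. For the two SCHFI scores used in Sample size it is about 8% to 10%. These figures assume two-sided tests, one group-by-phase test per score, a claim of success on any one score, equal correlations from 0 to 0.7, and the stated score counts. The rate would be higher only under per-visit testing.

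As a separate matter, the carer component of the primary outcome has conflicting descriptions and no settled direction, and is unavailable for patients without a carer.

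**What to change.** Choose one of two routes and state it in Outcomes, Sample size and Statistical analyses alike:
1. Keep several primary scores, list each one with its deciding contrast, and control the family-wise error at 0.05 with Holm.
2. Name one primary score, visit and contrast consistent with Sample size, and test the other scores in a fixed order. SCHFI maintenance is one candidate: it is already in the power statement and, unlike management, has no symptom restriction.

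Under either route, limit the unadjusted 0.05 sentence in Statistical analyses to what it validly covers, and state how the researcher's review is scored and analysed without a baseline.

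Reconcile the Abstract, Background, Study aims, Hypotheses, Table 1, carer measures and Outcomes on which carer score is primary and which direction is favourable, or move the CC-SCHFI to the carer outcomes.

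Cost: route 1 loses almost no power at the plan's stated effect size, but a noticeable amount if the true effect is smaller (step 6 of the working). Route 2 makes a self-report the sole primary in a trial whose participants know their allocation. The Discussion itself warns that self-report depends on memory and values the carer and nurse sources, so this is a real loss of weight on them. The trial is already recruiting, so the change should be made as a documented amendment.
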